#### Secondary research objectives

The secondary objectives are to assess differences in adherence to the advice and weight change from baseline to eight month follow-up in those receiving genetic test feedback and weight gain prevention advice compared with advice alone. We hypothesize that participants receiving genetic test feedback, regardless of risk status, will be more adherent to the advice and gain less weight over the study period than those receiving weight gain prevention advice alone. Within the group of participants receiving feedback and advice, we will also explore psychological reactions immediately after receiving genetic test feedback, and interactions between weight status and gene test status. We hypothesize that those receiving a higher-risk genetic test result will show higher negative affect but not higher fatalism in response to their genetic test result compared to those receiving an ‘average-risk’ genetic test result. We also predict that overweight participants receiving a ‘higher-risk’ result will value having an explanation for their weight more than normal weight participants, and that overweight participants will be more motivated to prevent further weight gain in response to a higher-risk genetic test result than those receiving an ‘average-risk’ result. All secondary objectives are exploratory, because of limited power.

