### Sample size and assumptions

A power calculation conducted *a priori* using *GPower* (version 3.1; http://www.psycho.uni-duesseldorf.de/abteilungen/aap/gpower3/download-and-register)showed that a total sample size of n = 340 should suffice to detect a small effect (η = 0.25) for motivation to prevent weight gain between ‘Feedback and Advice’ and ‘Advice Only’ group with 95% power or greater at the 5% significance level, accounting for an attrition rate of 60% (based on research with other student samples). We chose the small effect size based on data from the vignette study [9] and on *FTO*s moderate effects on weight.

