#### Secondary

Results from all secondary analyses will be considered as exploratory. One-way ANOVAs, followed by one-way ANCOVAs will be used to examine immediate psychological reactions to genetic test feedback in the sample overall once the AO group participants have received their genetic test results. Repeated-measures ANOVAs will be used to determine change in anthropometric measures within groups over time in the sample overall. Anthropometric differences between groups will be determined using one-way ANCOVA. Age, gender and baseline BMI will be included as covariates. Changes in diet quality, eating behavior and physical activity in the sample overall will be examined with repeated-measures ANOVAs. Changes between groups will be examined using one-way ANCOVAs, including age, gender and baseline BMI as covariates. Group differences in actual behavior change (as measured by adherence to the individual tips) will be assessed with a one-way ANCOVA. In addition, we will build an additive score of the total number of tips adhered to at least ‘occasionally’ and compare this in intervention and control group with a one-way ANCOVA. Age, gender and baseline BMI will be included as covariates. Bonferroni corrections will be used for multiple comparisons in all analyses. Within the ‘Feedback and Advice’ group, *FTO* status will be dichotomized into high/average risk, with those having at least one risk allele being classified as ‘higher-risk’. Ordinal regression analyses will be used to examine effects of risk status on motivation to control weight, as well as interactions between risk status and baseline BMI. Age and gender will also be included as predictor variables in the model. Finally, we will assess predictors of motivation to control weight with a multinomial regression analysis. We will include all potential predictors, including age, gender, *FTO* status, as well as stress, eating behavior, baseline BMI, and weight satisfaction.

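### Holm's step-down procedure would protect the secondary comparisons as well as the planned single-step Bonferroni and never reject fewer of them (a small, free improvement)

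*Protocol article*

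**What the plan says.** The multiplicity rule is one sentence in the Secondary subsection of Statistical analyses: "Bonferroni corrections will be used for multiple comparisons in all analyses". It follows a list of ANOVAs and ANCOVAs on reactions to feedback, anthropometry, diet, eating behavior, activity and adherence to the tips. That subsection opens with "Results from all secondary analyses will be considered as exploratory", and the Secondary research objectives section adds "All secondary objectives are exploratory, because of limited power".

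The primary analysis has its own subsection: one ordinal logistic regression of Feedback and Advice (FA) against Advice Only (AO), with no mention of a correction. Sample size and assumptions sizes that comparison "with 95% power or greater at the 5% significance level".

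**The concern.** The article names a specific procedure, single-step Bonferroni, for analyses that it says are short of power. Bonferroni holds every p-value in a family of m tests to 0.05/m. Holm starts at the same threshold and relaxes it after each rejection, with the same guarantee on the chance of any false rejection. Where several secondary effects are real, Bonferroni can therefore miss some that Holm would detect, and the stricter rule buys no further guarantee.

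At stake is some sensitivity in exploratory results. The conclusion on the primary aim is not affected.

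**Working it through.** **Level used for the primary test.** The article's own figure is "a total sample size of n = 340 should suffice to detect a small effect (η = 0.25) for motivation to prevent weight gain". Reading 0.25 as Cohen's f (a standardised difference of 0.5 for two groups), a two-group F test at an uncorrected two-sided 5% with 95% power needs 210 evaluable, and 210 × 1.6 = 336, within about 1% of 340. A one-sided test gives 174 × 1.6 ≈ 279, which does not match. The primary was therefore sized at two-sided 5% without correction. With one comparison, Bonferroni gives 0.05/1 = 0.05, the same level. (Multiplying by 1.6, rather than dividing by 0.4 to get 525, is a separate matter.)

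**Why Holm cannot do worse.** Order the p-values p(1) ≤ … ≤ p(m). Bonferroni rejects when p ≤ 0.05/m. Holm compares p(i) with 0.05/(m − i + 1) and stops at the first failure. For the seven tips listed under Adherence to the weight loss tips:

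- Bonferroni: 0.05/7 = 0.0071 for every test.
- Holm: 0.0071, 0.0083, 0.0100, 0.0125, 0.0167, 0.0250, 0.0500.

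No Holm threshold is below 0.05/7, so anything Bonferroni rejects, Holm rejects too.

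**Inputs for the size of the gain.**

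- Number of tests: 7, from the list of tips.
- Analysed: 800 × 0.4 = 320, or 160 per arm. This uses the planned enrolment and the 60% attrition in the sample-size section. It is before the exclusion of participants already controlling their weight.
- True difference 0.3 SD and correlation 0.5 between tests: assumptions, since the article gives neither.

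**Bonferroni per tip.** Expected test statistic = 0.3 × √(160/2) = 2.683. Critical value at 0.05/7, two-sided = 2.690. Power = Φ(2.683 − 2.690) = 49.7%, or 49.1% with the noncentral t distribution on 318 degrees of freedom.

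**Both methods, by simulation** of equicorrelated normal test statistics (mean power per real effect):

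| Real effects among 7 | Bonferroni | Holm | Gain (points) |
|---|---|---|---|
| 7 | 49.8% | 60.0% | 10.2 |
| 3 | 49.7% | 51.9% | 2.2 |
| 1 | 49.7% | 49.7% | 0 |

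No simulated data set had a hypothesis rejected by Bonferroni and not by Holm. With no real effects, the chance of any rejection was about 4% and identical for the two methods.

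**Range.** Correlation matters little: with all seven effects real, Holm gives 61% at correlation 0 and 59% at 0.8. Varying the other inputs, at correlation 0.3:

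| Setting | 7 real | 3 real | 1 real |
|---|---|---|---|
| 400 analysed, 0.3 SD | 62.2% v 73.8% | 62.1% v 64.7% | 62.0% v 62.0% |
| 320 analysed, 0.2 SD | 18.3% v 21.7% | 18.6% v 19.3% | 18.3% v 18.4% |

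(Bonferroni v Holm. The 400 reflects the loss of about half stated under Minimizing drop out.)

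**The case against.** Bonferroni is valid and prespecified, and the analyses it governs are twice declared exploratory. On this view, preferring Holm is a matter of taste. The ten-point gain needs every tip to have a real effect, and in sparser cases little or nothing is gained. The article also does not define its families, which is commonly left to a fuller plan.

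Most of this stands. Nothing is stated wrongly, the ten points are a best case, and the seven-tip family is an illustration. What does not follow is that the choice is neutral. The article fixes a procedure, and another gives the same guarantee with at least as many rejections for one changed sentence.

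A reader might infer something stronger: that the words about all analyses bring the primary test under Bonferroni, so that a primary p-value of, say, 0.03 could be called positive or negative at will. The documents do not support this:

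- The sentence stands under Secondary and is limited to multiple comparisons.
- The primary analysis is one FA v AO regression in a two-arm trial, so its divisor is 1.
- No passage pools primary and secondary tests into one family, and no divisor above 1 is given for the primary.

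The Primary outcome section does list a readiness item and three rated statements. Which of these feeds the regression is a separate question. The article nowhere says that they are tested as a family of four.

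**Conclusion.** The point holds as a free improvement of low severity. Holm keeps the family-wise guarantee of the planned rule and never rejects fewer hypotheses. On the assumed inputs, the gain per real effect runs from nil with one real effect, through about 2 points with three, to about 10 points with all seven. With 0.2 SD the best case shrinks to 3.4 points. The dominance of Holm needs none of these assumptions; only the size of the gain does.

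There is no contradiction over the primary threshold, which is 5% under both the sample-size text and the ordinary reading of the Bonferroni sentence.

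**What to change.** In the Secondary subsection of Statistical analyses, replace the Bonferroni sentence with:

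> Within each family of secondary comparisons, p-values will be adjusted by Holm's step-down procedure. The single primary comparison (FA v AO) is tested at the two-sided 5% level without correction.

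The second sentence changes nothing; it confirms how the sample-size and primary-analysis sections already read. The exploratory label stays.

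The change needs no new data or participants. Its one drawback is that simultaneous confidence intervals matching Holm are less simple than Bonferroni intervals. For these exploratory results, unadjusted 95% intervals can be reported and labelled as such.

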**Methods/design:**

First-year university students (n = 800) will be randomized to receive either 1) their personal genetic test result for a gene *(FTO)* related to weight gain susceptibility in addition to a leaflet with simple weight control advice (‘Feedback + Advice’ group, FA), or 2) only the leaflet containing simple weight control advice (‘Advice Only’ group, AO).

Motivation to avoid weight gain and active use of weight control strategies will be assessed one month after receipt of the leaflet with or without genetic test feedback. Weight and body fat will be measured at baseline and eight months follow-up. We will also assess short-term psychological reactions to the genetic test result. In addition, we will explore interactions between feedback condition and gene test status.

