#### Control group (‘Advice Only’ group)

Following baseline measurements, participants randomized to the ‘Advice Only’ control group will receive an email at the same time as the FA group informing them that they will receive their test result by the end of the academic year, resembling a ‘wait-list control’ group for the gene test feedback condition. The weight control advice leaflet will be attached to the email, matching the format of the intervention group. Ethical concerns about withholding weight control advice from individuals at increased risk of weight gain, and the likelihood of contamination between groups, led to the decision to send the leaflet to all participants and therefore not to have a ‘no treatment’ control group that receives neither leaflet nor genetic feedback. The gene test result will be sent out in identical format to the intervention group at the end of the academic year after collection of follow-up anthropometric data is complete.

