#### Primary

Ordinal logistic regression will be used to assess the difference in ‘Feedback and Advice’ *versus* ‘Advice Only’ group for motivation to prevent weight gain. Additional predictor variables will include age, gender and weight status at baseline, because these may influence results.

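### The announced feedback-by-gene interaction is in no specified model, and the effect of the risk result on motivation is examined only within the feedback arm, where genotype and result received coincide

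*Protocol article*

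**What the plan says.** The abstract of the protocol article (Methods/design) announces that "we will explore interactions between feedback condition and gene test status".

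The body specifies something else:

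- **Secondary research objectives.** Within the FA group, the article will explore "interactions between weight status and gene test status". It predicts that overweight participants will be more motivated in response to a higher-risk result than to an average-risk one.
- **Statistical analyses, Primary.** The ordinal model has group plus covariates: "Additional predictor variables will include age, gender and weight status at baseline, because these may influence results". It has no genotype term.
- **Statistical analyses, Secondary.** Within the FA group, FTO "status will be dichotomized into high/average risk, with those having at least one risk allele being classified as" higher-risk. Then "Ordinal regression analyses will be used to examine effects of risk status on motivation to control weight". The only interaction planned for this model is introduced by the words "as well as interactions between risk status and baseline BMI". The model also adjusts for age and gender.
- **Closing multinomial model, same section.** It lists FTO status among the predictors of motivation but names neither arm nor an interaction.

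Control participants are genotyped as well. For them, "The gene test result will be sent out in identical format to the intervention group at the end of the academic year", after the follow-up body measurements. The Randomization section places allocation before the DNA analyses.

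**The concern.** The article announces one interaction and specifies a different one. In the FA-only model the feedback condition is constant, so the announced interaction cannot be estimated there.

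The substitute contrast is not randomised. Everyone in FA with an A allele is told higher risk, and everyone with TT is told average risk. A difference in motivation could come from the message or from an association between genotype and wanting to control weight that would exist without any message. Such an association is plausible on the article's own account: the Background gives FTO modest effects on weight gain, and the age range was chosen because its association with BMI peaks in early adulthood.

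At stake is a question the Background raises directly: whether a higher-risk result motivates or induces fatalism, and whether a lower-risk result breeds complacency. Even with no genotype association, a difference within FA cannot tell motivated carriers from complacent TT participants, because neither group is compared with people who were not told.

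**Working it through.** **What each contrast estimates.** On the log odds scale, after the planned covariates, let γ be the carrier-versus-TT difference in motivation among people not told their result. Let δ₁ be the effect of feedback in carriers (told higher risk) and δ₀ its effect in TT participants (told average risk).

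- Carrier versus TT within FA (planned): γ + (δ₁ − δ₀)
- Carrier versus TT within AO (untold at one month): γ
- Arm × FTO interaction, the difference of these two: δ₁ − δ₀
- FA versus AO within carriers: δ₁; within TT: δ₀

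Only the last two lines are free of γ.

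**Inputs.** The Randomization section gives 400 per arm, 252 carriers and 148 TT (252/400 = 63%, 148/400 = 37%). Sample size and assumptions gives 60% attrition, which leaves 252 × 0.4 ≈ 101 and 148 × 0.4 ≈ 59 per arm. The article gives no precision or power figure for risk status or for an interaction, so there is none to reproduce.

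**Precision on the ordinal scale.** Whitehead's formula gives V = n₁n₂/(3n) × (1 − Σp³) and SE = 1/√V. The shares of the four responses are assumed: 0.35, 0.20, 0.10, 0.35. Then Σp³ = 0.09475 and 1 − Σp³ = 0.905.

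- Within FA: 101 × 59/(3 × 160) × 0.905 = 11.24, SE 0.298
- Carriers, FA v AO: 101 × 101/(3 × 202) × 0.905 = 15.24, SE 0.256
- TT, FA v AO: 59 × 59/(3 × 118) × 0.905 = 8.90, SE 0.335
- Interaction: √(0.256² + 0.335²) = 0.422, which is √2 × 0.298

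The article excludes participants who have controlled their weight for more than a month. If that is the assumed 35% in the fourth category, about 66 carriers and 38 TT remain per arm, with shares 0.54, 0.31, 0.15 and 1 − Σp³ = 0.811.

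| Contrast | SE, all responders | SE, after excluding 35% |
|---|---|---|
| Carrier v TT within FA | 0.30 | 0.39 |
| FA v AO, carriers | 0.26 | 0.33 |
| FA v AO, TT | 0.34 | 0.44 |
| Arm × FTO interaction | 0.42 | 0.55 |

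For 80% power at a two-sided 5% level, the interaction needs a ratio of odds ratios of about exp(2.80 × 0.42) ≈ 3.3, or exp(2.80 × 0.55) ≈ 4.7 after the exclusion.

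**Consequence of γ.** This uses a normal approximation on a standardised outcome before the exclusion. The within-FA SE is √(1/n_A + 1/n_T), with n_A carriers and n_T TT participants: 0.164 at 60% attrition and 0.104 with none. The feedback effect is set equal in both FTO groups (δ₁ = δ₀), and γ is assumed:

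| Assumed γ (SD) | Within-FA test significant, 60% attrition | Within-FA test significant, no attrition | Interaction test |
|---|---|---|---|
| 0.1 | 9% | 16% | 5% |
| 0.2 | 23% | 49% | 5% |
| 0.3 | 45% | 83% | 5% |

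**Price.** At 60% attrition the interaction SE is √2 × 0.164 = 0.232. For a true 0.5 SD difference, power is 86% within FA if γ = 0, against 58% for the interaction. For 0.25 SD it is 33% against 19%.

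**The case against.** The case on the other side has four parts.

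**Exploratory status and condensation.** All secondary objectives are declared exploratory because of limited power, and an article may leave the exact terms of an exploratory model to the full plan. This stands as a limit on severity. It does not remove the point: the article states an interaction in one place and spells out a different analysis in another, which is a mismatch rather than an omission.

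**The within-FA model matches its own objective.** The Secondary research objectives pose the question within FA, and the analysis follows. That is fair for a descriptive comparison. But the same section speaks of motivation in response to a higher-risk result, which is a claim about the effect of the result.

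**The planned covariates deal with the obvious route.** Baseline BMI, age and gender are in the model, and BMI is the likeliest path from an unknown genotype to wanting to control weight. This stands in part. What remains is only the association outside those variables, and the documents give no figure for it. It could be zero.

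**The hypothesis about risk status is already covered.** A reader might infer that the hypothesis that "participants receiving genetic test feedback, regardless of risk status, will be more adherent to the advice" also has no analysis. The documents do not support that firmly. It can be read as the pooled comparison of FA with AO, and the Secondary section contains those ANCOVAs for adherence and body measurements.

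**Conclusion.** The point holds as a moderate one. The announced arm × gene interaction appears in no specified model. For motivation, the only specified analysis of the risk result is a non-randomised contrast in which genotype and message cannot be separated.

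A reader might go further and infer that the effect of feedback itself is confounded with genotype. It is not: allocation precedes genotyping, and the primary FA versus AO comparison is randomised. Only the exploratory higher- versus average-risk contrast within FA is affected.

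The size of the distortion is unknown. The 9% to 45% range rests on assumed residual genotype shifts of 0.1 to 0.3 SD and on 60% attrition. The standard errors rest on assumed response shares, and the figures after exclusion on an assumed 35% excluded. The √2 ratio between the interaction and within-FA standard errors depends on neither, provided response shares and retention are similar in the two arms. Comparing FA with AO within genotype removes genotype confounding. It does not remove bias from attrition or from the planned exclusion.

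**What to change.** Add to Statistical analyses, Secondary, an exploratory ordinal model for motivation in both arms with arm, FTO status (any A versus TT), arm × FTO status, age, gender and baseline BMI. Report FA versus AO within each FTO group with confidence intervals, alongside the interaction estimate. Keep the within-FA contrast, labelled non-randomised and descriptive. Then the abstract and the analysis section agree.

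No new data are needed: both arms are genotyped, AO is still untold at one month, and recruitment is in progress, so the model can be prespecified now. The cost is precision. The interaction SE is about 1.4 times the within-FA SE (about 0.42 v 0.30, or 0.55 v 0.39 after the exclusion, under the stated assumptions). The plan should therefore say that a null interaction is not evidence of no difference.

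Do not add an arm × FTO × BMI test or a separate test in overweight participants. Both would be weaker still than an interaction that already has low power.

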## Discussion

The disappointing results from most trials of weight gain prevention warrant development of novel methods to engage individuals with weight control. Genetic test feedback has the potential to be a tool that could help raise awareness of susceptibility to weight gain. The increasing popularity of genetic testing to ‘personalize’ medicine makes evaluation of its effects imperative. The current trial uses a rigorous study design, taking ethical and practical concerns into consideration. For example, we chose to test the impact on motivation after one month instead of immediately after receiving feedback, to give participants sufficient time to think about their test results and to ask any questions. This may provide a more accurate measure of the effects of test feedback than the possibly transient ‘spur of the moment’ reactions occurring immediately after receiving the genetic test result. However, there are a number of limitations. The study uses a young, healthy, well-educated sample, which allows for investigating the effects of feedback but limits generalizability of the results to the wider population, particularly those with lower health literacy. Control over food choices in this study is limited due to the university setting (the majority of students live in catered halls). This may affect the ease with which weight gain prevention can be achieved and results may differ in settings where control over food intake is higher. Nonetheless, results from the current sample are of interest, particularly because they provide an indication for the effect of testing for prevention of unhealthy weight gain in a population where weight gain is common. With this study, we hope to provide a first indication of the potential benefits of inclusion of genetic testing into weight management advice, laying the groundwork for future research evaluating the clinical utility of genetic testing for the prevention of ill health.

